#### Sensitivity analyses

To assess the robustness of the results on cost-effectiveness, we will perform four sensitivity analyses. First, analyses will be performed using the complete cases only. Second, analyses will be performed in which the lost productivity costs will be calculated according to the human capital approach. In the human capital approach, total sick leave days are not fixed as in the friction cost approach, and elasticity is not required [25]. Third, analyses will be performed with sick leave and healthcare usage data that are related to subacute or chronic musculoskeletal pain. Fourth, the observed outliers with very high lost productivity will be excluded from the analysis.

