Vocational rehabilitation is a widely advocated intervention for sick-listed workers with subacute or chronic nonspecific musculoskeletal pain [9–12]. Vocational rehabilitation is “a multiprofessional evidence-based approach that is provided in different settings, services, and activities to working-age individuals with health-related impairments, limitations, or restrictions with work functioning and whose primary aim is to optimize work participation” [13]. In addition, work participation is conceptualized as the involvement in work roles or the lived experience of work. Work participation restriction refers to problems an individual may experience at work. Examples include number of hours lost from work (that is, absenteeism), underperforming job expectations, reduced desired employment (for example, part-time employment, short-term disability, long-term disability, premature retirement, or fewer working hours than desired), and reduced career growth [14]. However, in this paper, work participation (restriction) is expressed as the number of sick leave days due to subacute or chronic musculoskeletal pain. Research shows that vocational rehabilitation improves return to work [9–12, 15–22], and thus facilitates work participation. However, the dose-effect relation of vocational rehabilitation on work participation is unclear. Several reviews on the effectiveness of vocational rehabilitation on work participation for sick-listed workers with SMP and CMP show a wide range in treatment hours [9, 11, 20, 23]. In addition, a systematic review revealed a range of 6.4 to 196.8 hours in pain rehabilitation programs [23]. So far, only one randomized controlled trial has compared the dose-effect relation of vocational rehabilitation (VR) [16]. Sick-listed workers with CMP were classified at baseline as good, medium, or poor based on their prognosis for return to work (that is, return to work defined by the authors as absence of sick pay or related benefits in a given month), and were thereafter randomized to extensive VR (approximately 120 treatment hours), light VR (approximately 20 to 30 treatment hours), or care as usual (referred back to general practitioner). After 14 months follow-up, the participants classified with poor prognosis benefited most from the extensive VR, resulting in higher return to work rates, whereas patients classified with medium prognosis benefited from both the light and extensive programs on improving return to work rates. In another paper, but using the same study construct and population as in the Haldorsen trial [16], results were obtained without the prognosis on return to work (that is, good, medium, or poor) and on a follow-up period of two years. After 2 years follow-up, the light VR resulted in the highest return to work rates compared with usual care, but significance was only found in men. Additionally, the authors found no significant difference on return to work rates between light and extensive VR or between extensive VR and usual care [24].

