**Fig. 2 Fig2:**
[figure not shown]
Timing of data collection

**Table 1 Tab1:** Outcome measures for each of the measurement moments

Outcomes	Time measured			Follow-up					
	Baseline	Midterm	Discharge	2 months	4 months	6 months	8 months	10 months	12 months
	T0	T1	T2	T3	T4	T5	T6	T7	T8
Descriptive variables									
Demographic variables	x								
General perceived health	x								
Work-related psychosocial factors	x								
Self-efficacy of work participation	x								
Pain intensity	x		x						
Fatigue	x								
Work tolerance functions	x								
Outcome measures									
Primary									
Work participation^a^	x	x	x	x	x	x	x	x	x
Secondary									
Work ability	x		x			x			x
Disability	x		x			x			x
Physical functioning	x		x			x			x
Quality of life	x		x			x			x
Costs^a^									
Presenteeism	x	x	x	x	x	x	x	x	x
Health care usage	x		x		x		x		x

^a^The primary outcome *work participation* will also serve as a cost outcome (that is, absenteeism)

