#### Primary outcome

The primary outcome in this study is work participation expressed as total sick leave days due to subacute or chronic musculoskeletal pain. Total sick leave days will be calculated from the start of the intervention until 12 months follow-up after discharge. Sick leave will be measured using the absenteeism items of the iMTA (institute for Medical Technology Assessment) Productivity Cost Questionnaire (iPCQ) [34]. The questionnaire has a recall period of 4 weeks and measures sick leave on working days and on a generic basis (that is, the reason for sick leave is not asked). We have made slight adaptations to measure sick leave specifically (that is, related to subacute or chronic musculoskeletal pain, or other reasons such as flu), and we have added an item to assess the working hours at this moment: “Are you working for the full number of hours you were contracted for?” This question has three possible answers: “yes,” “no, I am partly at work,” and “no, I am on 100 % sick leave.” After the answer “no, I am partly at work” the participant is asked to fill in the number of hours he/she is working per week at that moment. The iPCQ is the result of combining two existing Dutch questionnaires (PRODISQ and SF-HLQ), and is recommended by the Dutch guideline for health economic evaluations [35]. The iPCQ has been translated by a professional language institution into a patient-friendly version using more simple language, thereby increasing the feasibility and validity of the questionnaire [34]. A population with mental health problems showed a satisfactory reliability regarding the iPCQ absenteeism items (icc 0.83) [36]. Until now, reliability of the iPCQ has not been tested in our study population. This needs to be done in the near future.

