
#### Cost outcomes

The following outcomes will be assessed to evaluate the cost-effectiveness of the 40-h VR compared with the 100-h VR:Absenteeism data will be derived from the work participation (that is, primary outcome) data in this study.Presenteeism will be assessed using the presenteeism items of the iPCQ [34]. The questionnaire measures the total days of mental or physical complaints at work, with a recall period of 4 weeks. The amount of work performed accompanied by mental or physical complaints is measured on a 0 to 10 response scale, where 0 represents “I couldn’t do anything,” to 5 “I could do about half of normal,” to 10 “I could do the same as normal.” A population with mental health problems showed good feasibility and validity [34], and moderate reliability for the number of days while impeded by mental or physical complaints (icc 0.56), and a satisfactory reliability for the efficiency rate (0 to 10) item (icc 0.73) [36].Healthcare usage will be assessed using the Trimbos iMTA questionnaire for measuring Costs of Psychiatric Illnesses (TiC-P), module 1 [36, 44]. A recall period of 4 weeks is used in this questionnaire. Visits and consultations of the following healthcare providers were measured: general practitioner, physiotherapist, manual therapist, exercise therapist, occupational therapist, psychologist, insurance physician, medical specialists in hospitals, hospitalization (number of days), occupational physician, social worker, and dietician. Additional items were alternative care, home care, medication use, and job-related care like job coaches, ergonomic changes at the work site and reintegration specialists. Slight adaptations in the context and scope of health care practitioners were made to better match TiC-P to the target population (that is, from psychiatry to pain and work). Another modification was that visits and consultations were measured in both generic and sickness-specific terms. Research shows that health care usage assessment by means of self-reported questionnaires is reliable [45]. A population with mental health problems showed good feasibility, promising construct validity, good agreement on medical resource use (yes/no), and sufficient test-retest reliability on the number of contacts with the health care providers [36]. Until now, reliability of the TiC-P has not been tested in our study population. This needs to be done in the near future.

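### As written, the sick-leave part of the third economic sensitivity analysis repeats the base case, and the sick leave collected for other reasons enters no stated analysis

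*Protocol article*

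**What the plan says.** All references are to the protocol article.

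- **Primary outcome.** The outcome is cause-specific: "The primary outcome in this study is work participation expressed as total sick leave days due to subacute or chronic musculoskeletal pain". The Background uses the same definition: "work participation (restriction) is expressed as the number of sick leave days due to subacute or chronic musculoskeletal pain".
- **Source of absenteeism.** Cost outcomes states: "Absenteeism data will be derived from the work participation (that is, primary outcome) data in this study". The footnote to Table 1 adds that the primary outcome "will also serve as a cost outcome (that is, absenteeism").
- **What is collected.** According to Primary outcome, the absenteeism items were adapted to "measure sick leave specifically (that is, related to subacute or chronic musculoskeletal pain, or other reasons such as flu"). Pain-related and other leave can therefore be separated or added together. For healthcare use, Cost outcomes says that "visits and consultations were measured in both generic and sickness-specific terms".
- **Third of four sensitivity analyses.** "Third, analyses will be performed with sick leave and healthcare usage data that are related to subacute or chronic musculoskeletal pain". The other three are complete cases, the human capital approach, and exclusion of outliers with very high lost productivity.

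**The concern.** A sensitivity analysis is informative only if it changes something. The third one is presented as a narrowing of sick leave and healthcare use to the pain condition, which presupposes a wider base case. For sick leave, the text gives a base case that is already narrow.

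Absenteeism enters the economic evaluation in three ways:

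- It is monetized as a benefit in the employer's cost-benefit analysis.
- It is listed among the indirect costs under the societal perspective. By inference it also enters the cost-utility analysis, whose own section does not list cost components.
- It is the effect in the cost-effectiveness ratio, where it is removed from the cost side.

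A reader of the results could take agreement between the base case and the third analysis as evidence that the cause of leave does not matter, although nothing about sick leave had been varied. Two analysts could also build different base cases from the same text. If the choice is made after the results are seen, it is open to challenge.

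**Working it through.** There is no figure in the plan to reproduce. The check traces one quantity through the document.

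**Notation.** For each participant, let P be pain-related sick leave days and O be sick leave days for other reasons. The adapted questionnaire records both.

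**Step 1: base case as written.** The primary outcome is P (Background; Primary outcome). Absenteeism is taken from the primary outcome (Cost outcomes), and the primary outcome itself serves as the absenteeism cost outcome (Table 1 footnote). So base-case absenteeism = P.

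**Step 2: third sensitivity analysis.** Sick leave is limited to the pain condition (Sensitivity analyses). So sensitivity absenteeism = P.

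**Step 3: difference as written.** P − P = 0 for every participant. Any valuation applied to identical days gives identical costs, so the change in monetized absenteeism is zero in both arms. The effect term of the cost-effectiveness ratio does not change either.

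**Step 4: the alternative reading.** If base-case absenteeism were all-cause, it would be P + O, and the third analysis would remove (P + O) − P = O. The between-arm difference in mean days would change by mean O in the 40-h arm minus mean O in the 100-h arm. The documents give no value for either mean, so this cannot be sized. In a randomized comparison it may be small, but the plan neither says so nor tests it.

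**Step 5: do the other sensitivity analyses use O?** Complete-case analysis changes who is included. The human capital approach changes how days are valued. Outlier exclusion removes participants. None of them changes the cause of leave, so O enters no stated analysis.

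**Step 6: what falls outside the point.**

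| Component | Scope as written | Can the third analysis differ from the base case? |
|---|---|---|
| Absenteeism | Pain-related in both | No |
| Healthcare use | Recorded generically and specifically; base-case scope not stated outright | Yes, if the base case is generic |
| Presenteeism | Any physical or mental complaint at work | Not named in the third analysis |
| Primary non-inferiority analysis | Pain-related | Not part of the economic sensitivity analyses |

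**The case against.** The strongest reply is that an all-cause base case was intended. Saying that absenteeism is derived from the work participation data could refer to the whole set of sick-leave answers, which includes other reasons, rather than to the pain-only total. The third analysis would then be a true restriction, parallel to its healthcare half, and the wording of Sensitivity analyses makes most sense that way. This may well be what was meant. But no sentence says so, and the Table 1 footnote makes the primary outcome itself the absenteeism measure. On this reading, the Cost outcomes sentence and the footnote are what need correcting.

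A second reply is that the choice between all-cause and condition-related absenteeism is a matter of scope. That stands: a pain-related base case is not an error in itself. The fault is that the stated check does not vary the scope of sick leave.

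A third reply is that in the cost-effectiveness analysis it is coherent to keep the effect equal to the primary outcome while only healthcare costs change. That also stands, but it does not help the employer analysis, where absenteeism is monetized.

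A reader might go further and infer that productivity loss from causes other than pain is never costed, or that the third analysis is empty. The documents support neither. Presenteeism is asked about any complaint and is costed under both perspectives, and healthcare use is also recorded generically, so the healthcare half can still move the result.

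**Conclusion.** Wrong as written, and limited to absenteeism. Following the Primary outcome section, the Cost outcomes section and the Table 1 footnote, the sick-leave part of the third sensitivity analysis equals the base case exactly, and leave for other reasons is collected but used nowhere. If the base case was meant to be all-cause, two of those places misdescribe it. Either way, the document needs a correction.

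The conclusion rests on reading the primary outcome and the footnote literally. It is a conflict between rules the article itself states, not a complaint about detail left to another document.

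The consequence is confined to the economic evaluation: directly the employer analysis, the listed societal costs and the effect side of the cost-effectiveness ratio, and by inference the cost-utility analysis. The Background attributes 48 to 88 % of costs to sick leave and productivity loss at work together, so the scope of absenteeism deserves a clear statement. That range does not show how much leave is due to other causes, and the size of the omission remains unknown. The primary non-inferiority conclusion does not depend on this point.

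**What to change.** State one base case for absenteeism in the economic evaluation and make the third sensitivity analysis the other. Either version works:

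1. All-cause absenteeism in the base case, with pain-related sick leave as the sensitivity analysis (the present wording of Sensitivity analyses then stands).
2. Pain-related absenteeism in the base case, with all-cause sick leave as the sensitivity analysis.

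Align Cost outcomes, the Table 1 footnote and Sensitivity analyses with the choice. State the base-case scope of healthcare use in the same sentence. Say whether the effect in the cost-effectiveness ratio stays at the pain-related primary outcome or changes with the sensitivity analysis. Leave the definition of the primary outcome as it is. Settle this before the economic data are analyzed, so that the base case is not chosen on the results.

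The cost is a few sentences and a little extra analysis. No new data are needed, because the adapted questionnaires already record both versions.

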### Sample size

A sample size of 174 is calculated to be sufficient (with a one-sided 95 % CI, 80 % power, alpha of 0.025, standard deviation of 80 and a margin of non-inferiority of 30 days) to establish non-inferiority of 40-h VR. The sample size calculation allowed for 15 % loss to follow-up - 10 % expected from comparable studies [18, 59, 60] and 5 % expected due to the extension of the program in the 40-h VR group. An intraclass correlation coefficient (ICC) of 0.05 is accounted for by the use of four rehabilitation centers with two clusters (40-h and 100-h VR) at each center [61, 62]. Because of the difference in program hours between 40-h and 100-h VR, we expect 40-h VR to benefit by 8 extra working days available during the intervention period. We accounted for this in the power calculation by using minus 8 as the expected mean difference between 40-h and 100-h VR. In our power calculation, we assumed a normal distribution of the primary outcome work participation. If the data on the primary outcome does not follow a normal distribution, we will perform log transformations. As previously stated, we will allow 28 % as the margin of non-inferiority when the data is log transformed.

According to the number of patients expected to be referred to the four participating rehabilitation centers per year (approximately 350), and after accounting for two-thirds of non-participation in the study according to Lasagna Law [63], we expect an inclusion of 115 participants per year for this study. Hence, our inclusion period will cover approximately 18 months, and the data collection period will cover 2 years and 9 months.

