### Non-inferiority hypothesis

A reduction in sick leave days of more than 30 days per year is deemed a clinically significant improvement on work participation [15, 17–19, 24]. A difference in sick leave days of 30 or fewer (from the start of the intervention until 12-months follow-up) between 40-h and 100-h VR is assigned as the margin of non-inferiority in this study. Our hypotheses are as follows:H0: μ1 - μ2 ≥30H1: μ1 - μ2 <30

H0 is the null hypothesis, and H1 is the alternative hypothesis, μ1 is the mean number of sick leave days in the 40-h VR group, and μ2 is the mean number of sick leave days in the 100-h VR group.

Non-inferiority is claimed if the upper bound of the one-sided 95 % confidence interval of the treatment effect difference (μ1 - μ2) on work participation does not exceed 30, which means that the risk of it being inferior is within acceptable boundaries [30]. We expect a normal distribution of the primary outcome work participation. If the data on the primary outcome does not follow a normal distribution, we will perform log transformations. The margin of non-inferiority will then be interpreted as a 28 % increase in the sick leave days’ difference of μ1 - μ2. We calculated this percentage as follows:$$ 30/107 = 28\ \% $$

where 30 denotes the margin of non-inferiority and 107 the expected mean days of sick leave in the 100-h VR arm [15, 17–19, 24] during the timing of the data collection, which equals approximately 15.5 months (intervention period of 3.5 months + the follow-up period of 12 months, see Fig. 2).

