### Randomization

An independent statistician prepared the randomization by using computer-generated randomization tables. To prevent unequal randomization, employees are pre-stratified by duration of sick leave (short-term <6 weeks or long-term ≥6 weeks) and whether they are on full-time (100 %) or part-time (≤99 %) sick leave. Block randomization with blocks of four will be applied to ensure equal group sizes within each stratum. A separate block randomization table is generated for each of the four participating vocational rehabilitation centers. For each stratum, the researcher will prepare opaque, sequentially numbered, and sealed coded envelopes, with a note for either the 40-h VR or 100-h VR. After the multidisciplinary screening (at baseline), the multidisciplinary screening team and rehabilitation physician will fulfil all study criteria. If participants meet all criteria, they will be allocated to 40-h or 100-h VR. Treatment allocation will be performed by a member of the multidisciplinary screening team (MST) at each center and can be performed at the center or via telephone (this will differ among the centers). The MST member hands over two envelopes (left over) of that stratum, and the patient is asked to pick one of the envelopes, open the envelope and sign the note. In the case of telephone allocation, the MST member will ask the patient to sign informed consent and to return it via a reply envelope. When the signed informed consent is received, the MST member will perform the treatment allocation without the patient. After randomization, a research assistant will make an appointment for the patient’s first intervention date.

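### N = 174 does not contain the inflation that an ICC of 0.05 requires for the eight clusters the protocol names, so the stated 80 % power is not secured

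*Protocol article*

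**What the plan says.** All inputs are in the protocol article.

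- Sample size: "A sample size of 174 is calculated to be sufficient", with "80 % power, alpha of 0.025, standard deviation of 80" and "a margin of non-inferiority of 30 days". The same sentence also refers to a one-sided 95 % confidence interval. A 15 % loss allowance is included.
- Sample size, on clustering: "An intraclass correlation coefficient (ICC) of 0.05 is accounted for by the use of four rehabilitation centers with two clusters (40-h and 100-h VR". Every centre thus contributes both clusters. No design effect and no number of patients per cluster is given.
- Sample size, on the assumed effect: the 40-h arm is expected to gain 8 available working days because its programme is shorter. "We accounted for this in the power calculation by using minus 8 as the expected mean difference between 40-h and 100-h VR".
- Non-inferiority hypothesis: "Non-inferiority is claimed if the upper bound of the one-sided 95 % confidence interval of the treatment effect difference" does not exceed 30.
- Randomization: individual patients are allocated in blocks of four from a separate table for each centre. One of the strata is "whether they are on full-time (100 %) or part-time" sick leave.
- Methodological considerations: differences between centres are to be handled by multilevel analysis and by giving both programmes at every centre.
- Interventions: both programmes are described as group-based.

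**The concern.** The power statement claims that an ICC of 0.05 has been allowed for, and it names the clusters as the two arms at each of four centres. With so few clusters each one is large, and a design effect depends on the number of patients per cluster. The margin between the uninflated sample size and 174 is far too small for that.

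If the ICC does act at that level, the trial has a much lower chance of showing non-inferiority than stated, and a failure to show it would be hard to interpret. The assumed −8 days adds to this. It moves the distance to the margin from 30 to 38 days and carries much of the stated power, yet the section gives no power for the case in which the two programmes lead to the same number of sick leave days.

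**Working it through.** **Inputs** (Sample size, Non-inferiority hypothesis): SD 80; margin 30; true difference −8, so distance to the margin 38; power 80 %; 15 % loss; ICC 0.05; 4 centres × 2 arms = 8 clusters; 1:1 allocation. Alpha is taken both as 0.025 (stated) and as 0.05 (literal reading of a one-sided 95 % interval).

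**1. Reproducing 174.** n per arm = 2 × SD² × (z₁₋α + z₀.₈)² / distance².
- Alpha 0.025: 2 × 6400 × (1.960 + 0.842)² / 38² = 69.6, so 70 per arm, 140 in total. Loss alone: 140 / 0.85 = 165, short of 174. With a factor of 1.05: 70 × 1.05 / 0.85 = 86.5, so 87 per arm and 174 in total.
- Alpha 0.05: 54.8 per arm. With a factor of 1.35: 2 × 54.8 × 1.35 / 0.85 = 174.1.

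Both routes reach 174. The protocol does not say which was used.

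**2. Design effect that 174 can hold.** Evaluable patients: 174 × 0.85 = 147.9.
- Alpha 0.025: 147.9 / 140 = 1.056.
- Alpha 0.05: 147.9 / (2 × 54.8) = 1.35.

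**3. Design effect for the clusters named.** Patients per cluster: 147.9 / 8 = 18.5. Design effect = 1 + (18.5 − 1) × 0.05 = 1.875. Neither value in step 2 comes near this. In the formula 1 + (m − 1) × 0.05 they correspond to m of about 2 and 8, not 18.5.

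**4. Power at N = 174.** SE = 80 × √(2 × DE / 73.95), and power = Φ(distance / SE − z₁₋α). Distances are 38, 34 and 30 for true differences of −8, −4 and 0.

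| Design effect | SE | Alpha | −8 | −4 | 0 |
|---|---|---|---|---|---|
| 1 (centre effect shared by arms) | 13.16 | 0.025 | 82.3 % | 73.4 % | 62.6 % |
| 1 | 13.16 | 0.05 | 89.3 % | 82.6 % | 73.7 % |
| 1.05 | 13.48 | 0.025 | 80.5 % | 71.3 % | 60.5 % |
| 1.05 | 13.48 | 0.05 | 88.0 % | 81.0 % | 71.9 % |
| 1.875 (arm within centre) | 18.01 | 0.025 | 56.0 % | 47.1 % | 38.4 % |
| 1.875 | 18.01 | 0.05 | 67.9 % | 59.6 % | 50.8 % |

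The rows with design effect 1 make no use of centre in the model. With centre fitted, power at −8 and alpha 0.025 is about 84 %.

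**5. Would more patients help?** With eight clusters, cluster size grows with N. Solving n / (1 + (n/4 − 1) × 0.05) = 69.6 gives n = 69.57 × 0.95 / (1 − 0.0125 × 69.57) = 507 per arm, or about 1,190 enrolled (2 × 507 / 0.85), at alpha 0.025. At alpha 0.05 it is about 389. At a true difference of 0 the target cannot be reached on either alpha: the effective n per arm cannot exceed 4 / 0.05 = 80, while 112 (alpha 0.025) or 88 (alpha 0.05) are needed.

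**The case against.** The strongest reply is that the ICC may describe variation between centres. The discussion of methodological considerations speaks of centres differing in logistics, facilities and methods, and each centre has its own randomisation table with both arms in it. A centre effect common to both arms then drops out of the comparison, 174 is slightly generous, and there is no shortfall at −8. This stands as a possible reading, so it cannot be concluded that the trial is underpowered. But it is not what the Sample size section describes. That section names the arms within centres as the clusters, and group-based delivery makes clustering at that level plausible.

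A reader might infer that the planners mistakenly used two, the number of clusters per centre, as the cluster size. The factor of 1.05 fits that, but the protocol prints no design effect, and alpha 0.05 with a multiplier of 8 reaches 174 as well. The derivation can only be inferred.

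A reader might also infer that the −8 is an error because patients on full-time sick leave cannot turn freed programme hours into work. The 60-hour difference between programmes is 7.5 days if a day is 8 hours (an assumption), so −8 does suppose that nearly all saved time becomes working time. But the value, its reason and its use are disclosed, sick leave status at entry is not fixed over the follow-up, and the realised share cannot be derived from the document. It is a planning assumption whose influence should be shown.

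Finally, a zero-difference miss rate of about 4 in 10 holds only at alpha 0.025. With design effect 1.05 and alpha 0.05 it is about 28 % (100 − 71.9).

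**Conclusion.** The statement that an ICC of 0.05 is accounted for is wrong as written. For the eight clusters named, the design effect is about 1.875, and power at −8 is about 56 % (alpha 0.025) or 68 % (alpha 0.05), below 80 % on either alpha. If the ICC is purely a centre effect, the same N gives about 82 % at alpha 0.025 and no inflation was needed. If only part of the 0.05 is specific to an arm within a centre, power lies between those ends. The protocol does not settle the level, so the claim is that 80 % is not secured, not that it is missed.

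Separately, the 80 % is conditional on the full −8. With design effect 1.05, half of it gives about 71 % and none about 61 % at alpha 0.025, or 81 % and 72 % at alpha 0.05.

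These figures assume SD 80, exactly 15 % loss, equal clusters and normal quantiles. With only eight clusters, normal quantiles favour the design when the arm-within-centre reading applies.

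**What to change.** Keep N = 174 and correct the text of the Sample size section:

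1. State the level at which the ICC of 0.05 acts and the matching design effect.
2. Restate the power at −8 accordingly: about 56 % at alpha 0.025 (68 % at 0.05) if it acts on arms within centres, or about 82 % at alpha 0.025 (89 % at 0.05) if it is a centre effect only, in which case no inflation should be claimed.
3. State which alpha applies, so that it agrees with the interval in the decision rule.
4. Report power at a true difference of 0 beside power at −8.

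Do not change how sick leave days are counted in order to support the −8, since that would alter the primary outcome.

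The cost is text only, with no added patients and no change to the design. The downside is a less favourable power statement, at 0 in any case and at −8 under the arm-within-centre reading.
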